**Methods:**

This program integrates fundamental movement skills training with cognitively challenging activities. Four classes per kindergarten will be randomly assigned to one of four conditions: (1) combined fundamental movement skills and cognitive challenge, (2) sedentary with cognitive challenge, (3) fundamental movement skills alone, or (4) sedentary without cognitive challenges. Each condition involves 30-minute sessions, three times per week, with a six-week washout period between the three-week intervention phases. The research team will use multiple objective measures and self-report measures, covering the elements and domains of the assessment of physical literacy and executive function. Three follow-up tests will be conducted within six months after the end of the intervention to evaluate the long-term impact of the program. Intervention implementation and fidelity will be assessed through focus group interviews with teachers and principals.

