
### Washout period

In a cluster randomized crossover (CRXO) design, washout periods need to be carefully set to minimize the impact of the effects produced by the previous intervention on the next intervention [43]. The carry-over effects of psychological or behavioral interventions are difficult to measure accurately, and the optimal duration for a washout period has not yet been clearly established. In a study published by a team of Stanford University researchers on the effects of digital physical activity intervention on daily steps, the crossover process of four interventions did not have a washout period [44]. Some previous crossover designs related to PA interventions agreed that it is appropriate to set a washout period equal to the duration of the intervention period [45–47]. In addition, there is a need to consider the impact of young children’s own rapid development of motor skills and cognition in non-intervention situations. Therefore, this study hypothesizes that the carry-over effects of the intervention on young children will be greater than the rest of the lifespan, that the duration of the washout period will be set to be twice the length of the intervention period (3 weeks for the intervention period and 6 weeks for the washout period), and that pre-tests and post-tests will be implemented at each stage of the intervention to ensure the accuracy of the measurements

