### Data collection procedures

Data collection will follow a cyclical pattern: 1-week pre-test, 3-week intervention, 1-week post-test, and 6-week washout. This cycle will be repeated three times, followed by a final post-test at week 38 and three follow-up tests at 8-week intervals (weeks 46, 54, and 62). See Table 1 for the detailed schedule. In the CRXO design of this study, from the cohort perspective, each cluster is required to receive all 4 interventions sequentially; from the cross-sectional perspective, each cluster is required to receive 4 different interventions each at the same time; thus, a total of 24 combinations of the intervention sequence are generated (4*3*2). Since the effect of the intervention sequence on the results of the study will not be considered, this study will use GraphPad Software to randomly select the combination of the intervention sequence to be used in the study.

**Table 1 Tab1:** Schedule of the cluster randomized crossover trial

Schedule of Interventions 2025–2026		
20/10/2025-26/10/2025	1 week	Pre-test 1
27/10–16/11	3 weeks	Intervention 1
17/11–23/11	1 week	Post-test 1
24/11/2025-4/1/2026	6 weeks (Including Public Holiday for Christmas)	Washout period 1
5/1–11/1	1 week	Pre-test 2
12/1–1/2	3 weeks	Intervention 2
2/2–8/2	1 week	Post-test 2
9/2–22/3	6 weeks (Including Public Holiday for Spring Festival)	Washout period 2
23/3–29/3	1 week	Pre-test 3
30/3–19/4	3 weeks	Intervention 3
20/4–26/4	1 week	Post-test 3
27/4–7/6	6 weeks	Washout period 3
8/6–14/6	1 week	Pre-test 4
15/6 − 5/7	3 weeks	Intervention 4
6/7–12/7	1 week	Post-test 4
13/7 − 6/9	8 weeks (13/7–31/8 for washout, 1/9 − 6/9 for test)	Follow-up 1
7/9 − 1/11	8 weeks (7/9–25/10 for washout, 26/10 − 1/11 for test)	Follow-up 2
2/11–24/12	8 weeks (2/11–17/12 for washout, 18/12–24/12 for test)	Follow-up 3

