### Data analysis

Descriptive statistics (means and standard deviations) will be calculated for all subscales across all measurements. Missing data will be calculated via maximum likelihood estimation via SAS version 9.4 (Cary, NC, USA). Given the characteristics of behavioral intervention research, we will not assume that the collected data will conform to a normal distribution and will be independent of each other. Therefore, a linear mixed effects (LME) model (from the R library NLME, R version 3.4.4) will be used to analyze the associations of different interventions with EF. The number of intervention days (time) was considered to have a possible association with intervention effects [72], so the interaction between the two will be included in the model. Fixed effects will include the intervention days and group, whereas the cluster (i.e., kindergarten) will be treated as a random effect. The LME model will be generated via the R NLME package. A p value less than 0.05 is recognized as a significant difference. Tukey’s honestly significant difference (HSD) test will be used to determine whether there is a significant difference between the interventions [73]. In addition, the false discovery rate-corrected *p* value will be used to determine if there is a statistically significant difference between the interventions. A value less than 0.05 is considered significant. Secondary outcomes (including cognitive difficulty, PA intensity, and teacher attendance) will be similarly assessed via the LME model.

An exploratory factor analysis of the possible static associations between FMS and EF will be conducted, which will be analyzed via partial least squares structural equation modeling (PLS-SEM), since PLS can maximize the prediction capability [74] and can address formative indicators as well as reflective indicators [75]. The relationship between PL and EF will be assessed via Pearson’s correlation coefficient. The effect size (Cohen’s *d*) will be calculated by dividing the difference between the post-intervention means of the two groups by their pooled standard deviation (SD).

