**Fig. 2 Fig2:**
[figure not shown]
Timeline of enrollment, interventions, and assessments of the “AMPLE” program. ^a ^In each 3-week intervention period, clusters receive one of four conditions: (1) FMS with cognitive challenge, (2) Sedentary with cognitive challenge, (3) FMS without cognitive challenge, or (4) Sedentary without cognitive challenge. As this is a cluster randomized crossover trial, each cluster receives all four conditions sequentially over the course of the study. ^b ^Arrow indicates continuous delivery of intervention.^c^ Implementation Fidelity includes workshops, logs, questionnaires and interviews for teachers.*Abbreviations*: *20mSRT*-*PREFIT* 20 m Shuttle-Run Test PREschoolers FITness Assessment, *Borg CR*-*10 * Borg Category-Ratio 10 Scale, *EmQue* Empathy Questionnaire, *FMS* Fundamental Movement Skills, *SCBE*-*30* Social Competence and Behavior Evaluation Scale, *SST* Stability Skill Test, *TGMD*-*3* Test of Gross Motor Development, Third Edition, *TRAILS*-*P *Trial Making Test for Preschoolers, *WLR * Word List Recall Test

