### Strengths and potential limitations

There are several strengths of this protocol. The four-arm cluster randomized crossover design is particularly suitable for educational research, as it effectively controls for cluster-level confounding variables by allowing each class to serve as its own control. This approach helps manage the influence of cluster-level confounding variables, such as the school environment or teacher characteristics, thereby increasing the statistical efficiency of the analysis [38]. Furthermore, this study addresses the issue of poor methodological quality that has been identified in previous intervention research [8] by employing a comprehensive assessment battery composed of validated and objective measurement tools. The implementation of the program by teachers within their natural kindergarten setting further enhances the ecological validity of the study, making its findings more translatable to everyday educational practice.

There are several foreseeable operational challenges. A principal concern is maintaining intervention fidelity, as it can be challenging to ensure that teachers accurately implement four different intervention programs over a 10-month period. To address this issue, this study included weekly teacher training workshops, a detailed course manual with clear instructions, and the use of questionnaires to monitor compliance. Teachers’ attendance at these workshops will also be recorded and analyzed as a potential factor influencing the effectiveness of the intervention. A 6-week washout period after each intervention also helped reduce teacher fatigue and boredom. Another challenge is the potential for carry-over effects. Although we set a washout period that is twice the intervention period, which is more conservative than previous CRXO studies, there is still no evidence to prove the optimal washout period setting for this type of cognitive or educational research. Finally, as a long-term intervention, there may be a high dropout rate and missing data, as well as a high probability of participant loss at the three follow-up tests after the intervention.

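### The mixed model's only random effect is for kindergarten, but classes are assigned and cross over and children are tested repeatedly, so its standard errors can be too large or too small

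*Protocol article*

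**What the plan says.** The Data analysis section of the protocol article specifies a linear mixed model for condition effects on executive function, and says that the secondary outcomes will be handled in a similar way. Its structure is given in one sentence: "Fixed effects will include the intervention days and group, whereas the cluster (i.e., kindergarten) will be treated as a random effect". An interaction between intervention days and group is also included. No class, class-by-period or child term is named, and no residual correlation structure, although the section says that independence will not be assumed.

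The design sections describe a different unit:

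- Abstract, Methods: "Four classes per kindergarten will be randomly assigned to one of four conditions".
- Strengths and potential limitations: the crossover works by "allowing each class to serve as its own control".
- Data collection procedures, cohort view: "each cluster is required to receive all 4 interventions sequentially". The Fig. 2 note agrees: "each cluster receives all four conditions sequentially over the course of the study".
- Data collection procedures, cross-sectional view, in the same sentence: "each cluster is required to receive 4 different interventions each at the same time". Here the cluster can only be the kindergarten.

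On repeated testing, the Washout period section says that "pre-tests and post-tests will be implemented at each stage of the intervention", and Data collection procedures adds three follow-ups: "This cycle will be repeated three times, followed by a final post-test at week 38 and three follow-up tests at 8-week intervals". Table 1 lists four pre-tests, four post-tests and three follow-ups.

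**The concern.** All four conditions run in every kindergarten at once, so the kindergarten is never the unit that receives a condition. A kindergarten intercept is reasonable, but it does not represent the level at which conditions are assigned and switched. Two kinds of dependence are then mishandled, with opposite effects.

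- **Stable differences between classes and between children.** In a crossover these cancel out of the condition contrast. If they are not modelled they stay in the residual, and the reported standard error is too large. The article justifies the design by its gain in power (Study design) and in efficiency (Strengths and potential limitations); the model as written does not deliver that gain.
- **Variation shared by the children of one class in one period**, such as how a teacher delivers a condition in those three weeks. This does not cancel. If it is not modelled, 11 children count as 11 independent observations, and the reported standard error is too small.

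At stake is the inference for every condition comparison made with this model, including the Tukey and false-discovery-rate results built on it.

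**Working it through.** **Inputs from the article.** 18 kindergartens, 4 classes each and 11 children per class: 18 × 4 × 11 = 792, as stated. There are 4 periods. Tests per child: 4 × 2 + 3 = 11. With all four conditions running at once in each kindergarten, each condition is observed in 18 × 4 = 72 class-periods, that is 72 × 11 = 792 child post-tests.

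**Inputs assumed.** The article gives no intraclass correlation or variance component. Total variance is set to 1 and kindergarten to 0.02; the rest is varied. Data are taken as balanced, with one post-test per period and no dropout.

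**Formulas, for the difference between two conditions.**

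- Reported variance (kindergarten only) ≈ 2 × (class + child + class-by-period + residual) / 792
- True variance = 2 × (11 × class-by-period + residual) / 792
- SE ratio (reported to true) = √[(class + child + class-by-period + residual) / (11 × class-by-period + residual)]
- Actual type I error ≈ 2 × [1 − Φ(1.96 × SE ratio)]

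**Example.** Class 0.03, child 0.50, class-by-period 0, residual 0.45: √(0.98 / 0.45) = 1.48. The reported SE is √(2 × 0.98 / 792) = 0.050 and the true SE is √(2 × 0.45 / 792) = 0.034.

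| Class | Child | Class-by-period | Residual | SE ratio, formula | SE ratio, simulated | Type I error, formula | Type I error, simulated |
|---|---|---|---|---|---|---|---|
| 0.03 | 0.50 | 0 | 0.45 | 1.48 | 1.48 | 0.4% | 0.4% |
| 0.03 | 0.50 | 0.02 | 0.43 | 1.23 | 1.20 | 1.6% | 1.8% |
| 0.03 | 0.50 | 0.05 | 0.40 | 1.02 | 1.00 | 4.7% | 5.2% |
| 0.05 | 0.30 | 0.05 | 0.58 | 0.93 | 0.92 | 6.8% | 7.1% |
| 0.05 | 0.50 | 0.10 | 0.33 | 0.83 | 0.81 | 10.5% | 11.6% |

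The simulated columns use 5,000 trials per row, with a Latin square of conditions within each kindergarten. A second simulation with slightly different components (kindergarten 0.03, child 0.30 to 0.40, class-by-period 0.10) gave 11 to 14%.

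**With the missing levels respected.** In the same five settings, an analysis of class-period means with class, period and condition effects has type I error of 4.9 to 5.4%. In balanced data it gives the same condition contrasts as a mixed model with class, class-by-period and child effects.

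**Break-even.** Setting the SE ratio to 1 gives class-by-period = (class + child) / 10. With class 0.03 and child 0.50 that is 0.053. Below it the plan is conservative; above it, liberal.

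**Power.** Take kindergarten 0.03, class 0.05, child 0.50, class-by-period 0 and residual 0.42. The true SE is √(2 × 0.42 / 792) = 0.033, so 80% power corresponds to an effect of (1.96 + 0.84) × 0.0326 = 0.09 SD. At that effect the kindergarten-only model has about 43% power, or about 40% if a 0.5 SD developmental trend also stays in the residual. The planned f = 0.3 implies, for four groups, a largest difference of at least 2 × 0.3 = 0.6 SD. In this scenario the kindergarten-only model already exceeds 99% power at 0.2 SD.

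**The case against.** **This is detail for the analysis plan.** A condensed article that names one random effect need not exclude others, and nlme supports nested effects and within-group correlation. This would carry weight if the article were silent. It is not: it states which level is the cluster, and that level conflicts with its own design sections. The degrees-of-freedom method, the choice of package and whether to adjust for the pre-test are matters for the analysis plan, and are no part of this point.

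**The variance components are assumed.** This stands. Type I error of 12 to 14% needs class-by-period variance near 0.10, for which the article offers no support. With class 0.05 and child 0.50 the model is liberal only above (0.05 + 0.50) / 10 = 0.055.

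**The model may already carry a period effect.** This stands in part. Intervention days (time) is a fixed effect, and if it means elapsed study time it absorbs some developmental trend. The article does not say how it is coded, so a missing period term is not established. Because conditions run concurrently within a kindergarten, a common trend would add noise rather than bias in balanced data.

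**A stronger reading.** A reader might infer that every standard error and p value in the trial is wrong, or that power is halved. The article supports neither. The two errors can cancel, as the third row of the table shows. The Pearson correlations, the PLS-SEM and the Cohen's d formula do not use this model. The halved power arises at about 0.09 SD, less than a sixth of the 0.6 SD that the planned effect implies.

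**Conclusion.** The concern holds in a limited form. The stated random-effects structure does not match the units that are assigned, cross over and are measured repeatedly, so inference on condition effects from this mixed model is not valid in general. The direction cannot be determined from the article and may differ between outcomes such as the shuttle run, movement skills, word recall and parent questionnaires. Over the assumed ranges the reported standard error is about 1.5 to 0.8 times the true one, and type I error about 0.4% to 12–14% at nominal 5%. The planned standard errors are right only when class-by-period variance is about (class + child) / 10, which nothing in the design ensures.

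These sizes rest on assumed components, 11 children in every class, balanced data without the 20% dropout that the article anticipates, and one post-test per period as the response. The full mixed model was not itself fitted; the comparator was the balanced-data equivalent. The power loss is real but matters only for effects much smaller than the one planned for. The mismatch of levels itself depends on none of these assumptions.

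**What to change.** 1. Define the cluster as the class throughout, and reword Data collection procedures so that the word no longer means class in one clause and kindergarten in the next.
2. In Data analysis, keep the kindergarten effect and add random effects for class within kindergarten, class-by-period and child. An equivalent within-child correlation structure would also serve.
3. Include period as a fixed effect, and state how it relates to intervention days (time): whether that variable is elapsed study time, days within a period, or pre-test versus post-test.

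The cost is a reworded analysis section and a few lines of code, with no new data and no change to conduct. Child and period are crossed within class, which is awkward to code in nlme, so the team should confirm before analysis that its software fits the chosen structure.

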### Participants

The study will include typically developing kindergarten children aged 3–5 years. Children aged 6 years will be excluded to avoid attrition due to their transition to primary school. The inclusion criteria are as follows: (1) Participants must be aged between 3 and 5 years (preschoolers). (2) Participants must attend a kindergarten in each of the 18 administrative districts in Hong Kong. (3) Participants must be free of any illness or disability that might interfere with their ability to complete the FMS, physical activity, daily tasks, or cognitive tasks required for the intervention. (4) Prior to enrollment in the intervention, informed consent signed by a parent or guardian must be obtained. The exclusion criteria are as follows: (1) Participants out of the age range of 3–5 years. (2) Participants who cannot attend kindergarten regularly. (3) Participants with known medical conditions or disabilities that would limit their participation in completing the FMS, physical activity, daily tasks, or cognitive tasks required for the study intervention and assessments. (4) Participants who did not provide consent from their parents or guardian.

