##### Fundamental movement skills (FMS)

The Test of Gross Motor Development Third Edition (TGMD-3) will be used to test participants’ FMS, which is specifically designed for children aged 3–10 years. As a procedure-oriented assessment test tool, it can evaluate the specific performance and completion process of children’s movements, and the operation process is simple and easy to observe. Therefore, it is widely used in the assessment of children’s FMS. TGMD-3 consists of a locomotor skills test and an object control skills test, which together have 13 movements (run, gallop, hop, skip, jump, slide, two-handed strike, one-handed strike, dribble, catch, kick, overhand throw, and underhand throw). The participants will be asked to watch a skill demonstration and be allowed to take a practice test before completing two formal tests. Proficiency the test will be assessed, with 3–5 movement criteria for each move. If a performance criterion for a skill is met, a score of “1” is given; if it is not met, the score is “0”. Each item will be tested twice, and the score will be accumulated for each item. The maximum total original score for the locomotor skill subscale is 46 points, and the maximum score for the object control skill subscale is 54 points. The higher the score is, the better the performance [54]. The assessments will be videotaped and scored by trained professionals [55].

Since the TGMD-3 does not include the assessment of stability skills in young children, the stability skill test (SST) will be used [56]. This test has been used for the assessment of 556 young children and was found to be a reliable scale (α = 0.81) [57]. The SST consists of three parts (rock, log roll and back support), and there are also 3–5 criteria for each move, with each movement tested twice. The final score of the two tests will be added to obtain the final score of the stability skill. The higher the score is, the better the stability skill [56].

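### The unadjusted Pearson correlation between physical literacy and executive function leaves age uncontrolled across ages 3–5, so shared growth is likely to inflate the association

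*Protocol article*

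**What the plan says.** All of the following is from the protocol article.

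- **Data analysis, on dependence:** "we will not assume that the collected data will conform to a normal distribution and will be independent of each other". This is the stated reason for a linear mixed model for EF. For that model, "Fixed effects will include the intervention days and group, whereas the cluster (i.e., kindergarten) will be treated as a random effect".
- **Data analysis, on the motor-cognitive link:** "An exploratory factor analysis of the possible static associations between FMS and EF will be conducted", to be carried out by partial least squares structural equation modelling (PLS-SEM). Then: "The relationship between PL and EF will be assessed via Pearson", with the correlation coefficient as the whole of the stated method. The section does not say which PL score or which test occasion enters, and it attaches no significance rule to this coefficient.
- **Participants:** the sample is "typically developing kindergarten children aged 3–5 years".
- **Washout period:** the design has to allow for children's "own rapid development of motor skills and cognition in non-intervention situations".
- **Outcome measures:** the motor score is described on its raw scale ("The maximum total original score for the locomotor skill subscale is 46 points"). Working memory is a count of words recalled, and the flexibility and inhibition tasks yield completion time and errors. No age-standardised score is mentioned.

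**The concern.** A Pearson coefficient has no place for age. If older children in a 3–5-year sample both move better and score higher on EF tasks, the two scores correlate even when children of the same age show no link at all. The usual test and interval for the coefficient also treat every pair of scores as independent. The section declines to make that assumption when it picks the mixed model, yet names a method that ordinarily relies on it a paragraph later.

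The Abstract gives better understanding of motor-cognitive connections as an aim. The Discussion says that the study can supply evidence for or against movement skill as a starting point of EF. An age-driven coefficient could be read as support for that idea when it shows only that children grow.

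**Working it through.** **Inputs from the article.** Planned sample 18 × 4 × 11 = 792, which reproduces. The assumed 20% dropout leaves 792 × 0.8 = 633.6, about 634. The significance level is 0.05; I take it as two-sided and apply it to this coefficient by assumption. The article states no figure for the PL-EF correlation, so there is none to reproduce.

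**Inputs assumed.** The correlation *a* of each score with age is not in the documents. I take it as equal in size for PL and EF, with no PL-EF link given age, and vary it. For completion time and errors the sign reverses but the size does not.

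**1. Smallest significant correlation.** From t = r√(n−2)/√(1−r²), |r| must exceed 0.070 at n = 792 and 0.078 at n = 634.

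**2. Correlation produced by age alone.** r = *a* × *a* = *a*². To reach 0.070 takes *a* = √0.070 ≈ 0.26 on each side.

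**3. Chance of p<0.05 with no direct link.** By Fisher's z, the test statistic is centred on atanh(r)·√(n−3), and both tails beyond ±1.96 are counted. Example for *a* = 0.3, n = 792: r = 0.09; 0.0902 × √789 = 2.53; 2.53 − 1.96 = 0.57; probability about 72%.

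| *a* | induced r | n = 792 | n = 634 |
|---|---|---|---|
| 0.1 | 0.01 | 6% | 6% |
| 0.2 | 0.04 | 20% | 17% |
| 0.3 | 0.09 | 72% | 62% |
| 0.4 | 0.16 | 99.5% | 98% |
| 0.5 | 0.25 | ~100% | ~100% |

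**4. Clustering alone, no age effect.** For a correlation between two clustered scores that are truly unrelated, the variance is inflated by about 1 + (m−1) × ICC_PL × ICC_EF. The familiar 1 + (m−1) × ICC is the factor for a mean and does not apply. With m = 11 per class:

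- ICC 0.02 on both scores: 1 + 10 × 0.0004 = 1.004
- ICC 0.10 on both: 1 + 10 × 0.01 = 1.10
- ICC 0.20 on both: 1 + 10 × 0.04 = 1.40

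Simulated false-positive rates of the plain Pearson test (the ICCs are assumptions):

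- 72 classes of 11: about 5–6% at ICC 0.05–0.1, and 10% at ICC 0.2
- 18 kindergartens of 44: about 6% at ICC 0.05, 9% at 0.1 and 20% at 0.2

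**5. If occasions were pooled as independent rows.** Table 1 has four pre-tests, four post-tests and three follow-ups, so up to 11 per child. Simulated false-positive rates for 8 or 11 occasions and within-child correlation 0.3–0.7 run from about 14% to 39%. In terms of effective size, 792 × 11 = 8,712 rows become 8,712/(1 + 10 × 0.4²) ≈ 3,350 at a within-child correlation of 0.4, and 8,712/(1 + 10 × 0.8²) ≈ 1,180 at 0.8.

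**6. After adjustment for age.** In the simulation with 72 classes of 11 and age uniform over three years, partialling out age brings the false-positive rate to about 4–7% at class ICC 0–0.1. It stays at about 9–11% at ICC 0.2. Age adjustment does most of the work, but clustering should be handled as well.

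**The case against.** Several points on the other side are sound.

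- **An article leaves covariates to the full plan.** True, and the silence of the PLS-SEM sentence on age and clusters is therefore weak evidence. Pearson for PL-EF is different: it is a stated method, and a fuller plan that adjusted for age would have to replace it.
- **The coefficient is peripheral.** It is in neither research question and in none of H1–H5. The companion FMS-EF analysis is called exploratory, and the Discussion assigns the cognitive-engagement test to the four-arm comparison. This stands and lowers the importance.
- **PL is broader than motor skill.** It also covers empathy and social scales rated by parents or teachers, and accelerometer activity. Nothing in the article says that these rise steeply with age, so the growth argument is firm only for the motor components.
- **As a description, r needs neither normality nor independence.** True. Those matter for its test and interval. Age confounding affects the interpretation of the coefficient either way.

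A reader might also infer more than the article supports:

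- That the section declares the data non-normal and dependent. It only declines to assume otherwise, and non-normality matters little at this sample size.
- That age will certainly yield a significant result. That depends on age correlations the article does not give; at 0.1–0.2 the chance is 6–20%.
- That class clustering alone seriously distorts the test. At class ICC up to 0.1 it hardly does.
- That all 11 occasions will be pooled. The article does not say so, and its description of the FMS-EF associations as static points towards a cross-sectional analysis.

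**Conclusion.** The point holds in limited form. The stated method for the PL-EF relationship cannot separate a motor-cognitive link from children growing older, and the article itself supplies the grounds for expecting that confounding: the age range, the raw scores and the acknowledged natural growth. Inflation is likely for the motor components of PL. A significant result with no direct link becomes more likely than not at an assumed age correlation of 0.3 on each side, and nearly certain at 0.4. Dependence is a secondary issue that becomes material only at higher class ICCs, with kindergarten-level ICCs of about 0.1 or more, or if occasions are pooled. The age correlations and ICCs are assumptions throughout. The randomised comparisons and H1–H5 are untouched, so this is a modest but worthwhile correction to an analysis that bears on the stated motor-cognitive aim.

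**What to change.** Replace the plain Pearson coefficient with an association adjusted for age in months at one named occasion, preferably Pre-test 1, before any condition has been delivered. Take it from a mixed model with class and kindergarten random effects, or from a partial correlation with cluster-robust intervals; either is adequate. State which PL score is used. Treat the PLS-SEM in the same way, with age as a control and inference that respects clusters. If several occasions are used, add a child effect and report within-child and between-child associations separately. Label the result exploratory.

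The cost is a change of analysis wording, plus holding age in months rather than only whole years. The reported association will probably be smaller and its interval somewhat wider. The change can be made before any outcome data are examined, and it does not alter the sample size or the randomised comparisons.
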